## Abstract

**Background:**

Adhering to a Mediterranean Diet (MedDiet) is associated with a healthier cardiometabolic profile. However, there are limited studies on the MedDiet benefits for non-Mediterranean racial/ethnic minorities, for whom this diet may be unfamiliar and inaccessible and who have a high risk of chronic diseases.

**Objectives:**

To describe the study design of a pilot trial testing the efficacy of a MedDiet-like tailored to adults in Puerto Rico (PR).

**Methods:**

The Puerto Rican Optimized Mediterranean-like Diet (PROMED) was a single-site 4-mo parallel two-arm randomized pilot trial among a projected 50 free-living adults (25–65 y) living in PR with at least two cardiometabolic risk factors (clinicaltrials.gov registration #NCT03975556). The intervention group received 1 individual nutritional counseling session on a portion-control culturally-tailored MedDiet. Daily text messages reinforced the counseling content for 2 mo, and we supplied legumes and vegetable oils. Participants in the control group received cooking utensils and one standard portion-control nutritional counseling session that was reinforced with daily texts for 2 mo. Text messages for each group were repeated for two more months. Outcome measures were assessed at baseline, 2 and 4 m. The primary outcome was a composite cardiometabolic improvement score; secondary outcomes included individual cardiometabolic factors; dietary intake, behaviors, and satisfaction; psychosocial factors; and the gut microbiome.

**Results:**

PROMED was designed to be culturally appropriate, acceptable, accessible, and feasible for adults in PR. Strengths of the study include applying deep-structure cultural components, easing structural barriers, and representing a real-life setting. Limitations include difficulty with blinding and with monitoring adherence, and reduced timing and sample size. The COVID-19 pandemic influenced implementation, warranting replication.

**Conclusions:**

If PROMED is proven efficacious in improving cardiometabolic health and diet quality, the findings would strengthen the evidence on the healthfulness of a culturally-appropriate MedDiet and support its wider implementation in clinical and population-wide disease-prevention programs.

## Introduction

Cardiometabolic health may be maintained by adhering to a healthy dietary pattern. A well-studied pattern is the Mediterranean diet (MedDiet) characterized by mainly consuming plant-based foods, including fiber-rich cereals, fruits, vegetables, olives, nuts, and seeds; consuming legumes, nuts, fish, and eggs as primary sources of protein; using olive oil; and consuming dairy products in moderation [[1], [2], [3]]. Alcoholic beverages—predominantly wine—are permitted in moderation [[1], [2], [3]]. Multiple studies have shown that adhering to a MedDiet is associated with a lower risk of CVD and cerebrovascular disease, several types of cancer, type 2 diabetes (T2D) and glycemic dysregulation, and better cognitive function and mental health [[4], [5], [6], [7]].

One seminal clinical trial testing the efficacy of the MedDiet on cardiometabolic risk factors was conducted in Spain between 2003 and 2012. The Prevención con Dieta Mediterránea (PREDIMED) was a multicenter, randomized controlled clinical trial that aimed to assess the effects of the MedDiet on primary prevention of CVD [8]. The study randomly assigned participants with a high risk of CVD a MedDiet supplemented with either extra virgin olive oil or mixed nuts (that is, walnuts, hazelnuts, almonds) or a reduced-fat control diet [9]. The trial showed benefits of the MedDiet within 3 mo, with significant reductions in plasma glucose, systolic blood pressure, and the ratio of total cholesterol-to-high-density lipoprotein cholesterol (HDL-C) in both the olive oil group and the nuts group, and C-reactive protein (CRP) in the olive oil group, compared with the control diet [10]. Compared with the control diet, long-term data from PREDIMED showed lower blood pressure and reduced risk of major cardiovascular events and T2D for participants in the olive oil or nuts groups [[11], [12], [13]]. The health benefits of a MedDiet have been linked to beneficial changes to the gut microbiome and its metabolites [14].

PREDIMED’s use of olive oil and nuts responds to their status as highly consumed traditional foods in countries bordering the Mediterranean Sea [[1], [2], [3]] and their high content of healthy fatty acids and antioxidants. However, studies on the feasibility and benefits of the MedDiet for non-Mediterranean cultures are limited [15, 16]. This limitation is salient for marginalized and underserved populations with a higher risk of chronic diseases. For example, individuals living in the United States (US) territory of Puerto Rico (PR) have high prevalence of cardiometabolic conditions, including an estimated 16%–26% of adults with T2D, 40% with hypertension, and 68% classified with overweight or obesity [[17], [18], [19]]. Adults in PR have unhealthy dietary patterns characterized by low intake of fruit, vegetables, and whole grains and a high intake of sweets and sugary beverages [20]. Observational studies among Puerto Rican adults suggest that following a Mediterranean-like diet comprised of traditional foods from PR is associated with lower abdominal obesity and body mass index (BMI), less insulin resistance, reduced inflammation, and improved cognitive function [[21], [22], [23]]. Yet, adherence to a MedDiet-like and its potential translation into health benefits have not been tested in Puerto Ricans.

Multiple agencies and committees, including the US Dietary Guidelines for Americans, the American Heart Association, and the World Health Organization, advocate for including nutrient-dense food and beverage choices that reflect personal and ethnic or cultural preferences [[24], [25], [26]]. These calls-to-action highlight the need for culturally-tailored programs that improve upon the existing evidence, leverage available food systems, and value cultural traditions of diverse communities. Ethnically-tailored interventions can be more effective than general dietary messages [[27], [28], [29]]. Thus, reporting the details of a cultural adaptation is essential to inform future processes in other populations. This report describes the study design of a pilot trial that aimed to examine the efficacy of a MedDiet-like tailored to adults in PR by using culturally appropriate foods and strategies for reducing cardiometabolic risk.

## Study Protocols

### Study design

The Puerto Rican Optimized Mediterranean-like Diet (PROMED) was a single-site 2-mo parallel two-arm randomized pilot and feasibility trial. The design included an in-person baseline nutritional counseling session among free-living adults (25–65 y) living in PR with at least two cardiometabolic risk factors, followed by text messages with content from the counseling session sent daily for 2 mo (delivery phase) and the same texts repeated daily for two more months (reinforcement phase) (Figure 1). Eligible participants in both the control and intervention groups were asked to attend a baseline, 2- and 4-mo visit for clinical measurements and questionnaires. One week after the baseline visit, the intervention group received one 1-h nutritional counseling session for a portion-control MedDiet-like tailored to adults in PR and a supply of vegetable oil and legumes to last for the first 2 mo. The control group received one 1-h nutritional counseling session for a standard portion-control diet and cooking utensils. A duration of 4 mo for the study was selected, based on early results of the PREDIMED trial that reported significant cardiometabolic improvements at 3 mo [10].

**FIGURE 1 fig1:**
[figure not shown]
PROMED protocol flowchart. PROMED, Puerto Rican Optimized Mediterranean-like Diet.

All data collection and procedures were conducted at FDI Clinical Research (FDI), an independent research center and medical care facility in San Juan, PR. FDI is associated with multiple research and clinical institutions and a network of primary care clinics across the archipelago of PR to facilitate recruitment. The Institutional Review Boards of Harvard TH Chan School of Public Health (protocol # IRB19-0184) and Ponce Health Sciences University in PR (protocol #1905013193A001) approved this study. The study was registered at clinicaltrials.gov NCT03975556. The study was conducted from July 2019 to June 2021. The SPIRIT reporting guidelines on study methodology only (no results) were used [30].

### Primary and secondary outcomes

Similar to a previous study [31], the primary outcome of PROMED was a composite cardiometabolic improvement score representing the summed number of improved cardiometabolic risk factors out of the 10 factors that were part of the eligibility criteria; the score has a plausible range of 0–10. Improvement was defined by clinically-meaningful decreases of *1*) waist circumference ≥ 1 cm; *2*) BMI ≥ 1 kg/m^2^; *3*) systolic blood pressure ≥ 5 mmHg; *4*) diastolic blood pressure ≥ 5 mmHg; *5*) plasma glucose ≥ 1 mg/dL; *6*) hemoglobin A1c ≥ 0.5%; *7*) plasma triglycerides ≥10 mg/dL; *8*) total cholesterol ≥ 10 mg/dL; and *9*) LDL-C ≥ 10 mg/dL; or an increase of [8] HDL-C ≥ 5 mg/dL [[32], [33], [34], [35], [36], [37], [38], [39], [40]]. A composite score was selected to account for baseline variability in cardiometabolic risk profiles. Furthermore, the selected markers are routinely measured in standard laboratory tests, and the predefined improvements are clinically meaningful in reducing the risk of chronic disease, facilitating the potential for clinical translation.

Secondary outcomes included changes in the individual cardiometabolic risk factors plus weight, dietary intake, overall diet quality, diet satisfaction, dietary behaviors, and psychosocial factors (e.g., depressive symptoms, stress). An exploratory aim was conducted to assess changes in the gut microbiome profile, based on previous literature suggesting associations between a MedDiet, legumes and oils, and gut microbiota composition and microbial functions [[41], [42], [43], [44]].

### Recruitment

Recruitment was done by posting flyers and posters in the main areas of the partner clinics; direct contact with patients and visitors to the partner clinics, where trained research assistants visited the waiting room and lobbies to distribute flyers to all individuals present and answer questions about the study; advertising in community locations and events (e.g.,., health fairs, festivals, supermarkets, shopping centers, parking lots) and social media (Facebook); and [4] through referrals from other participants.

Interested individuals contacted the study and were screened for potential eligibility using a phone-administered screening questionnaire. Potential eligibility was initially assessed based on *1*) age 25–65 y at the time of enrollment; *2*) noninstitutionalized (that is, not committed to an institution at the time of enrollment; such as prison, in-patient hospital, or treatment center); *3*) living in PR at the time of recruitment and for at least the previous year and not planning to move from PR within the next 6 mo; *4*) able to answer questions without assistance (that is, no severe psychological disorder or mental and/or physical disability that would prevent completion of interview); *5*) having a cellphone with the capacity to receive text messages and being willing to receive daily text messages from the study; and *6*) self-reporting at least two of five cardiometabolic conditions (elevated waist circumference, overweight or obesity, prediabetes, hypertension or use of blood pressure medication, dyslipidemia (high triglycerides or high LDL-C or low HCL-C or use of lipid-lowering medication).

If eligibility was probable based on these criteria, the individual was invited to a baseline visit where the research assistants used a scripted guide with clear, concise points to explain the study’s purpose, risks, and benefits, and any answer questions. Participants had the option of having a health proxy in the room during this process. Written informed consent to participate was obtained, including authorization to publish anonymized results as aggregated data. At the baseline visit, interviews and clinical and laboratory measurements were conducted to confirm the cardiometabolic conditions for eligibility, defined as waist circumference ≥94 cm in men or ≥80 cm in women; BMI ≥25 kg/m^2^; measured high systolic blood pressure (≥120 mmHg) or diastolic blood pressure (≥80 mmHg) (or use of blood pressure medication); measured prediabetes (fasting plasma glucose of 100 to 125 mg/dL (5.6 to 6.9 mmol/L) or hemoglobin A1C of 5.7 to 6.4% (39 to 47 mmol/mol); and measured total cholesterol ≥200 mg/dL or triglycerides ≥150 mg/dL or LDL-C ≥130 mg/dL or HDL-C <40 mg/dL, or use of lipid-lowering agents.

Individuals were excluded from the study for several reasons: *1*) self-reported physician-diagnosed type 1 or type 2 diabetes or use of diabetes medication or had a measured fasting plasma glucose ≥126 mg/dL (7.0 mmol/L) or hemoglobin A1C ≥ 6.5% (48 mmol/mol) at the baseline visit; *2*) reported current pregnancy; *3*) reported condition that would influence eating behaviors or nutritional status (e.g., Chron disease, inflammatory bowel disease, celiac disease, liver disease, kidney disease, cancer, diverticulitis, nut allergy, severe food allergies, or aversions); and *4*) intolerance or allergies to legumes (that is, beans and nuts) or vegetable oils (that is, soybean, olive, canola). These exclusion criteria were asked at subsequent visits, and individuals were withdrawn from the study if they answered affirmatively to any of these questions.

The blood test results of potentially-eligible individuals were received within 1 wk of the baseline visit. The values were used to confirm eligibility. If a person was deemed ineligible based on measured laboratory values, the individual was immediately informed and withdrawn from the study. Eligible participants were invited to complete the study examinations and surveys at FDI.

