### Randomization and data collection

Confirmed, eligible, and consented participants were randomly assigned to one of the two study groups (control or intervention) in a 1:1 allocation ratio. These participants were randomized using sex stratification (40% males and 60% females) and permuted blocks with random block sizes. For this randomization scheme, a sequence of block sizes was randomly generated in which allowable blocks were a random mix of sizes 2 or 4 participants. Thus, half of the participants within each block were randomly assigned to the control group and the other half to the intervention group.

Trained research assistants conducted all visits in a single private room at FDI. Research assistants were bilingual (English and Spanish) and trained in culturally sensitive interviewing, clinical protocols, data collection, data entry, confidentiality, and safety measures. Each clinical visit lasted ∼2 h. The counseling session lasted 1 h. Participants were compensated for their time up to $150, such that they received $50 at each of the three examination visits, with no monetary incentive at the counseling session. At the counseling session, participants received a bag with food (intervention group) or cooking utensils (control group). A light, healthy snack, and water were provided after each visit.

Participants were allowed to pause or terminate the interviews at any time. In such case, the participant was contacted up to five times within the subsequent 14 d to complete the pending questionnaires or measurements. Participants remained enrolled in the study for its duration (4 mo) unless they actively left the study, had a new ineligibility factor, or lost contact. All interview questions and outcome measures at 2  and 4 mo were assessed using the same protocols at baseline.

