### Statistical Analysis

Table 4 shows the minimum detectable effect sizes estimated for primary and secondary outcomes for the original sample size (n = 100) and adjusted sample size after COVID-19 protocols (n = 50), accounting for 10% loss-to-follow-up, using ANCOVA test [101] with 0.05 Type I error and 80% power.

**TABLE 4 tbl4:** Minimum detectable effect sizes (4 mo means adjusted for baseline) for primary and secondary outcomes for PROMED, using ANCOVA test for 80% power and 5% Type I error rate

	Mean (SD) at baseline	Empirical Corr. b∖w baseline and 4 mo values	MDE for n = 90 (45 per arm)	MDE for n = 44 (22 per arm)
10-item cardiometabolic improvement score	5.4 ± 1.4	0.94	0.28	0.40
Weight (lbs.)	201.2 ± 42.3	0.97	6.07	8.68
Waist circumference (cm)	42.9 ± 4.9	0.92	1.13	1.62
BMI (kg/m^2^)	34.2 ± 6.6	0.86	1.99	2.84
Systolic BP (mmHg)	123.4 ± 17.1	0.80	6.06	8.66
Diastolic BP (mmHg)	80.4 ± 9.3	0.49	4.79	6.85
Total cholesterol (mg/dL)	196 ± 46.5	0.59	22.17	31.71
LDL-C (mg/dL)	123.4 ± 37.4	0.83	12.32	17.62
HDL-C (mg/dL)	48.9 ± 12.4	0.83	4.08	5.84
Triglycerides (mg/dL)	118.2 ± 73.0	0.74	28.99	41.47
Glucose (mg/dL)	101.6 ± 29.4	0.80	10.42	14.90
Hemoglobin A1c (%)	6.0 ± 1.3	0.77	0.49	0.70
Diet quality (score)	35.2 ± 3.7	0.85	1.15	1.65
Diet satisfaction (score)	94.9 ± 18.9	0.85	5.88	8.41

BP, blood pressure; PROMED, Puerto Rican Optimized Mediterranean-like Diet. ∗The results account for 10% loss-to-follow-up for original sample sizes of n = 100 and n = 50. ∗∗The minimum detectable effect sizes (MDE) by the ANCOVA approach is calculated based on $MDE=\frac{4{\left(Z_{1-\frac{\alpha }{2}}+Z_{\beta }\right)}^{2}\left(1-Corr^{2}\right)SD^{2}}{n}$, where n is the sample size (active arm + control arm) after accounting for loss-to-follow-up, Corr is the correlation coefficient between the baseline and 4 mo values, SD is the standard derivation for the baseline value, $Z_{\tau }$ is the $\tau^{th}$ lower-quantile of the standard normal distribution, α=0.05 is the type I error rate, and β=0.8 is the power.

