The primary analysis is intention-to-treat. Data analysis will follow the Consolidated Standards of Reporting Trials (CONSORT) guidelines [102]. Flowcharts will include the number of participants at each stage, including screened, eligible, randomized, and followed-up. At the 4-mo follow-up, the mean cardiometabolic improvement score for participants in the intervention arm versus the control arm will be compared using a two-sample *t*-test. If randomization does not control for differences between the treatment and control groups on baseline characteristics, those differences will be statistically controlled for using multivariable regression modeling. Secondary analysis will compare the change in individual cardiometabolic risk factors and dietary and psychosocial factors between intervention and control groups using an ANCOVA test. Repeated measures analysis will test differences in 2- and 4-mo outcomes. Prespecified subgroup analyses will be conducted by sex-at-birth, BMI status, pre-existing cardiometabolic profile, COVID-19 period (pre- vs. at-pandemic), and adherence status. Missing data and loss to follow-up will be corrected. Two-sided 0.05 type I error threshold for statistical significance will be used.

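### Table 4's HbA1c SD cannot occur, and its glucose SD is highly implausible, under the trial's own diabetes exclusion, so both stated detectable differences are probably too large

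*Protocol article*

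**What the plan says.** The Recruitment section excludes people with "self-reported physician-diagnosed type 1 or type 2 diabetes or use of diabetes medication", and also anyone who "had a measured fasting plasma glucose ≥126 mg/dL (7.0 mmol/L) or hemoglobin A1C ≥ 6.5% (48 mmol/mol) at the baseline visit". The laboratory limits are enforced: "If a person was deemed ineligible based on measured laboratory values, the individual was immediately informed and withdrawn from the study". Only confirmed eligible participants are then randomized, "in a 1:1 allocation ratio". Every participant therefore starts below 126 mg/dL and below 6.5%.

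The Statistical Analysis section gives minimum detectable differences in Table 4, "using ANCOVA test [101] with 0.05 Type I error and 80% power". The footnote states that "SD is the standard derivation for the baseline value" and that "The results account for 10% loss-to-follow-up for original sample sizes of n = 100 and n = 50". The two rows at issue are:

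- **HbA1c:** 6.0 ± 1.3%, correlation 0.77, detectable difference 0.49 (n=90) and 0.70 (n=44).
- **Glucose:** 101.6 ± 29.4 mg/dL, correlation 0.80, detectable difference 10.42 (n=90) and 14.90 (n=44).

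The article does not say which sample supplied these means, SDs and correlations, and it describes no adjustment for the exclusion.

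**The concern.** An exclusion at a fixed ceiling limits how far baseline values can spread. The two SDs look too large for a population cut off at 6.5% and 126 mg/dL. Read as normal curves, they put about 35% of people at or above the HbA1c limit and about 20% at or above the glucose limit, and none of those people may be enrolled.

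The detectable difference is proportional to the SD, so an SD from a wider population carries straight into the printed figure. Table 4 is the article's only statement of what the trial can show on these two outcomes. A reader using it to judge a null result on glucose or HbA1c would be working from figures that belong to a different population.

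**Working it through.** **Inputs.** SDs, correlations and n come from Table 4. The ceilings come from the Recruitment section. Error rate and power are 0.05 and 80%, and the analysis paragraph confirms the sidedness: "Two-sided 0.05 type I error threshold for statistical significance will be used".

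**Step 1: reproduce the printed figures.** MDE = 2 × (1.960 + 0.842) × SD × √((1 − r²)/n).

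- HbA1c, SD 1.3, r 0.77: 0.490 at n=90 and 0.701 at n=44.
- Glucose, SD 29.4, r 0.80: 10.42 at n=90 and 14.90 at n=44.

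All four match. The formula printed under Table 4 lacks the square root; taken literally it gives about 222 for glucose and 0.49 for HbA1c at n=44. The tabulated values include the root, so this is a separate slip. The arithmetic is right for the inputs used; the question is the inputs.

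**Step 2: can these SDs occur under the ceilings?** For a variable bounded between m and M with mean μ, SD² ≤ (M − μ)(μ − m).

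- HbA1c: 1.3² = 1.69 ≤ 0.5 × (6.0 − m) requires m ≤ 2.62%. Taking the highest admissible reading as 6.4% instead of 6.5% requires m ≤ 1.78%. With an assumed floor of 4.0% the largest possible SD is √(0.5 × 2.0) = 1.00; with 4.5% it is 0.87. Even if the mean is left free, the SD cannot exceed half the range: (6.5 − 4.0)/2 = 1.25.
- Glucose: 29.4² = 864.4 ≤ 24.4 × (101.6 − m) requires m ≤ 66.2 mg/dL. At that floor everyone must sit at one of two values: (101.6 − 66.2)/(126 − 66.2), about 59%, at the ceiling and the rest at 66. With an assumed floor of 70 the largest possible SD is 27.8; with 60 it is 31.9.

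**Step 3: what spread is plausible?** Truncating Table 4's own normal curves at the exclusion limits gives an SD of 0.66% (assumed floor 4.0%) and 15.2 to 17.4 mg/dL (assumed floors 70 and 60). A uniform spread over 4.0 to 6.5% gives 0.72, and over 70 to 126 mg/dL gives 16.2.

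**Step 4: restated differences.** The documents give no SD or correlation for people without diabetes, so the following inputs are assumptions.

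| Outcome | Assumed SD | Correlation | MDE, n=44 | MDE, n=90 |
|---|---|---|---|---|
| HbA1c (%) | 0.3 to 0.7 | 0.77 (as printed) | 0.16 to 0.38 | 0.11 to 0.26 |
| HbA1c (%) | 0.3 to 0.7 | 0.50 | 0.22 to 0.51 | 0.15 to 0.36 |
| Glucose (mg/dL) | 8 to 16 | 0.80 (as printed) | 4.1 to 8.1 | 2.8 to 5.7 |
| Glucose (mg/dL) | 8 to 16 | 0.50 | 5.9 to 11.7 | 4.1 to 8.2 |

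The printed values are 0.70 and 0.49 for HbA1c, and 14.90 and 10.42 for glucose.

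**The case against.** The strongest objection is that SD and correlation cannot be moved separately. The ANCOVA figure depends on the residual SD, SD × √(1 − r²). In a linear model with constant residual variance, selecting people on the baseline value leaves the residual SD unchanged, because the correlation falls as the SD does. The detectable difference would then stay as printed.

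Part of this stands: the correlation would probably fall, so the gain is smaller than a change in SD alone suggests. Full cancellation is implausible here. The residual SDs implied by Table 4 are 1.3 × √(1 − 0.77²) = 0.83% and 29.4 × 0.6 = 17.6 mg/dL. Both exceed the whole baseline SD expected after truncation (0.66%; 15.2 to 17.4 mg/dL). They could hold only if 4-month values spread well beyond baseline. Under Table 4's own formula, even r = 0 gives 2 × 2.802 × 0.66/√44 = 0.56% and, for SDs of 15.2 to 17.4, 12.8 to 14.7 mg/dL at n=44, all below the printed figures.

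It can also be said that both outcomes are secondary, that the error probably runs in the cautious direction, and that the target fell from 100 to 50 because of budget and timeline (section on the impact of the COVID-19 pandemic). All of that stands. It limits the consequence but does not make the rows right.

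**Conclusion.** The point holds for both rows, with different force. The HbA1c SD cannot occur at any plausible floor. The glucose SD is highly implausible. The stated differences do not describe the eligible population and are probably too large. On the assumptions in the table, the n=44 figures would be about 0.16 to 0.51% and 4 to 12 mg/dL. The exact size cannot be settled from the documents.

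Four stronger readings are tempting but not supported:

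- **That the glucose SD is mathematically impossible.** It is not if values reach about 66 mg/dL or lower.
- **That the figures are wrong by a fixed multiple, or would inflate a later trial's sample size about tenfold.** (1.3/0.4)² is 10.6 only with the correlation held at 0.77. With r = 0.5 the ratio is (0.701/0.293)², about 5.7, and the 0.4 is itself assumed. Nothing says a later trial would reuse these inputs.
- **That 0.70% shows the trial could not detect the article's own 0.5% HbA1c improvement.** The 0.5% is a cut-off for scoring one person as improved; Table 4 gives a difference between arm means.
- **That the source sample is known to include people with diabetes, or that the trial enrolled them.** The first is a likely inference. The second would follow only if the rows were the trial's own baseline data, which the article does not say.

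**What to change.** Re-estimate the SD and the baseline-to-4-month correlation together in people who meet the Recruitment criteria (glucose below 126 mg/dL, HbA1c below 6.5%, no diagnosed diabetes or diabetes medication), and restate both rows at n=90 and n=44. If the reference sample cannot be split, print a range under stated assumptions. In either case add a footnote naming the reference sample. If the rows turn out to be the trial's own baseline data, they and the exclusion criteria must be reconciled.

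The cost is two table rows and a footnote. Conduct, sample size and the primary analysis are unchanged.
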